# 10.0 DATA COLLECTION AND MANAGEMENT

## 10.1 Data management

All clinical data will be recorded onto standardised case record forms by study clinicians. Laboratory data will be recorded in a laboratory record book by the study laboratory technicians and then transferred to the case record forms by the study clinicians. Data will be transferred from the case record forms into a computerised database (EPI INFO 6.04) by data entry personnel and will be double entered to verify accuracy of entry. Two back-up files of the database will be stored on compact discs after each data entry session. For quality control, check programs will be written into the database to limit the entry of incorrect data and ensure entry of data into required fields.

## 10.2 Data quality assurance and monitoring

All members of the study team will be educated in the study protocol prior to the onset of the trial. The study clinicians will complete case record forms at each patient visit. These forms will be reviewed by the study co-ordinator and site supervisors from the core facility for completeness and accuracy. For quality control of thick blood smear slide readings, expert microscopists who will be blinded to the patient’s treatment group will review a random sample of approximately 10% of slides. Study group meetings will be conducted by the co-ordinator once a week to assess progress of the study, address any difficulties, and provide performance feedback to the members of the study group. In addition members from the core facility will make regular visits to active study sites as needed.

## 10.3 Records

Case record forms will be provided for each subject. Participants will be identified by their initials and study identification number on the case record form. Patient names will not be entered into the computerised database. All patient record forms will be kept in individual files in a secure filing cabinet in the study clinic. All corrections will be made on case record forms by striking through the incorrect entry with a single line and entering the correct information adjacent to it. The correction will be initialled and dated by the investigator. Any requested information that is not obtained as specified in the protocol will have an explanation noted on the case record form as to why the required information was not obtained. Additional records will be kept in the clinical and laboratory record books at the core facility in Kampala. The investigators will allow all requested monitoring visits, audits or reviews.

# 11.0 LABORATORY PROCEDURES

## 11.1 Blood smears

Thick and thin blood smears will be stained with 2% Giemsa. Thick blood smears will be evaluated for the presence of parasitemia, including asexual forms and gametocytes. Parasite densities will be calculated from thick blood smears by counting the number of asexual parasites per 200 leukocytes (or per 500, if the count is <10 parasites/200 leukocytes), assuming a leukocyte count of 8,000/l. A thick blood smear will be considered negative when the examination of 100 high power fields does not reveal asexual parasites. Thin blood smears will be evaluated to determine parasite species.

## 11.2 Haemoglobin measurement

Haemoglobin will be measured from fingerprick blood samples using a portable spectrophotometer (HemoCue, Anglom, Sweden).

## 11.3 Molecular studies

Blood samples will be collected from patients on days 0, 2, 3, 7, 14, 21, 28 and on any unscheduled day that the patient presents with clinical deterioration or recurrent fever. Blood will be placed onto filter paper in approximately 25 ul aliquots per blood spot (4 blood spots per sample). The samples will be labelled, air-dried and stored in small, sealed sample bags at ambient temperature. Parasite DNA will subsequently be removed from the filter paper and prepared for molecular analysis using a chelex extraction method. Genotyping of parasites collected at baseline (day 0) and during follow-up will be done to distinguish between true recrudescence and reinfection with new parasites. Briefly, the block 3 region of the merozoite surface protein-2 gene will be amplified using nested PCR and characterized based on sequence and size polymorphisms identified by restriction endonuclease digestion and gel electrophoresis. Genotyping patterns on the day of repeat therapy will be compared with those at treatment initiation using GelCompar II software (Applied Maths). This laboratory work will be conducted in the UCSF laboratory directed by [name] and in the Makerere University laboratory directed by [name].

# 12.0 PROTECTION OF HUMAN SUBJECTS

## 12.1 Institutional Review Board (IRB) review and informed consent

This protocol and the informed consent documents, including any additional educational or recruitment material, will be reviewed and approved by the institutional review board of the Ugandan National Council of Science and Technology and the UCSF Committee for Human Research before the trial begins. Any amendments or modifications to this material will also be reviewed and approved by the IRBs prior to implementation.

## 12.2 Risks and discomforts

### 12.2.1 Privacy

Care will be taken to protect the privacy of subjects, as described in this protocol. However, there is a risk that others may inadvertently see patients’ medical information, and thus their privacy compromised.

### 12.2.2 Risks of randomization

This will be a randomized trial, and some treatment arms may prove to be more or less efficacious, more or less well tolerated, and/or more or less safe than others. Thus, there is the risk that patients will be randomized to less efficacious, less well tolerated, and/or less safe treatment regimens.

### 12.2.3 Fingerprick blood draws

Risks include pain, transient bleeding and soft-tissue infection.

### 12.2.4 Risk of amodiaquine

AQ has been described as “very well tolerated” for routine use, [27] and it was widely used for chemoprophylaxis against malaria in the past. However, prophylactic use was discontinued due to rare instances of agranulocytosis, aplastic anaemia, and hepatotoxicity, principally associated with use for malarial chemoprophylaxis in travellers. [7, 27] Reported rates of serious reactions to AQ in the UK were 1:2100 blood dyscrasias, 1:31,000 deaths from blood dyscrasias, and 1:15,650 serious hepatotoxicity. [28] Toxicities with short-term use for treatment are expected to be much lower, although data are limited. [7-11] In a review of 40 published and unpublished clinical trials, no severe or life-threatening adverse event was noted.[7] Considering tolerability in 488 AQ-treated patients, gastrointestinal toxicities and pruritis were most commonly reported, and the incidence of adverse events was similar among patients treated with AQ, CQ, and SP.[7] In Uganda, no serious toxicities were observed with AQ monotherapy (131 treatments). [11]

The neurological effects of artemisinins have been very extensively studied. In mice, rats, dogs, and monkeys, high dosages of intramuscular artemether and arteether produce an unusual and selective pattern of damage to certain brainstem nuclei, particularly those of the auditory and vestibular systems [36-47]. AS is transformed in vivo to dihydroartemisinin, which is the most neurotoxic of the artemisinin derivatives [48-50]. However, in the animal models, orally administered AS and dihydroartemisinin are considerably less neurotoxic than intramuscular artemether or arteether. Differences in toxicity are explained by differences in pharmacokinetics of different compounds and different routes of administration [40, 44, 46, 51]. Neurotoxicity results from the long-lasting blood concentrations that follow intramuscular injection of the oil-soluble compounds, artemether and arteether. Oral administration of artemether or arteether, which provides much more rapid absorption and elimination than intramuscular dosing, leads to markedly less neurotoxicity in mice, although oral artemether can be made more neurotoxic by giving the drug in small repeated doses to simulate the constant exposure that follows intramuscular injection [44]. Artesunate is much less toxic than arteether in rats when administered intramuscularly [45] or orally [41, 46, 52]. Importantly, with high dose intramuscular injections of artemether and arteether, clinical assessment of mice was a sensitive indicator of neurotoxicity; no mice with normal clinical exams showed histopathology [50].

In animals, there is clear evidence of death of embryos and some evidence for morphological abnormalities when artemisinin derivatives are administered in early pregnancy.[15] In addition, when artemisinins are given later in pregnancy, there is some evidence of adverse effects on fetal body weight and survival. Data on administration of artemisinin compounds during the second or third trimesters (607 pregnancies) do not suggest evidence of treatment-related adverse pregnancy outcomes, and similar data in 124 first trimester pregnancies indicated normal outcomes. However, few pregnancies have been evaluated, and further investigation on the reproductive safety of artemisinins is needed.

The artemisinin derivatives are remarkably well tolerated in humans. In a clinical safety review of 108 studies including 9,241 patients, no serious adverse events or significant toxicity was reported [14]. In addition, a systematic review of artemisinin derivatives for treating uncomplicated malaria, including 41 studies of 5,240 patients, showed no evidence of harmful effects related to artemisinin derivatives [53]. Clinical studies have shown no convincing evidence for neurotoxicity after treatment with artemisinin derivatives, though neurological effects of acute malaria are common. One letter described ataxia and slurred speech after AS therapy, but these findings were consistent with the course of severe malaria [54]. To specifically evaluate for potential artemisinin-associated auditory toxicity in humans, van Vugt et al. performed clinical neurological evaluations, audiometry and early latency auditory evoked responses in 79 patients treated with multiple doses of artemether or artesunate and 79 matched controls in Thailand, and no evidence of auditory toxicity was detected [32]. Comparisons of patients who had received multiple courses of artemisinin derivatives with age-matched untreated controls showed no significant differences in clinical, audiometric, or auditory evoked potential measurements [30, 32]*.* Even considering the most worrisome dosing regimen, there is no evidence that clinical use of intramuscular artemether has caused neurotoxicity. In a new report, four independent neuropathologists examined the brains of patients who died after treatment with intramuscular artemether, and there was no evidence for the characteristic pattern of neuropathological change seen in the animal studies [55]. These results suggest a wide margin of safety for artemisinins in clinical use, particularly when given orally, particularly for water soluble compounds, and most particularly for the most widely studied water-soluble agent, AS.

### 12.2.6 Artemether-Lumefantrine (Coartemether)

Coartemether (Coartem and Riamet; Novartis) has been extensively studied through GCP standardized preclinical and clinical trials and was added to the WHO Essential Medicines List in 2002 [56]. It has been approved for use against malaria in both developing and developed (e.g. Switzerland) countries. The drug appears to be very well tolerated, especially in comparison to other antimalarials and antimalarial combinations including chloroquine, quinine, and mefloquine+artesunate. A clinical safety review of children under 12 years of age showed that the most common adverse events were abdominal pain, cough, anorexia, headache, vomiting, and diarrhea (all seen in 5-12% of subjects). [57]

An integrated review of toxicity in 1869 patients (611 under age 13) showed the most commonly reported adverse events were gastrointestinal disturbances (abdominal pain, anorexia, nausea, vomiting diarrhea), headache, and dizziness. Rash and pruritis were reported in <2% of patients. No serious or persistent neurological toxicities were linked to coartemether therapy. Of 20 severe adverse events in 1869 patients, 19 were likely attributable to underlying malaria or concomitant illness, and one was possibly related to coartemether use (hemolytic anaemia in a 35-year-old 13 days after the last administered dose) [58]. One concern addressed in studies of coartemether was possible cardiac arrhythmogenic potential based on similarities in the chemical structures of lumefantrine and halofantrine. Halofantrine can cause defects in cardiac conduction, particularly a marked QT prolongation that can produce arrhythmias. In 713 patients treated with lumefantrine and followed with serial electrocardiograms, no adverse clinical cardiac events were recorded. Although trials have been limited to date, no serious cardiotoxicity or neurotoxicity has been reported with the use of coartemether [20, 22, 32, 59].

### 12.2.7 Risk of Quinine

Quinine is the standard drug for the treatment of severe malaria throughout Africa and is also the standard drug for the treatment of falciparum malaria in the U.S. It will be the treatment for patients who fail therapy with any study regimen. Quinine can commonly cause tinnitus, headache, nausea, dizziness, flushing, and visual disturbances. These symptoms, termed “cinchonism”, do not warrant discontinuing therapy unless they are severe. Less common toxicities include vomiting, diarrhea, and abdominal pain. Rare toxicities include skin rashes, urticaria, angioedema, bronchospasm, hemotologic abnormalities (hemolysis, leukopenia, agranulocytosis, and thrombocytopenia). Quinine can cause hypoglycemia, especially in pregnancy. Cardiovascular toxicity is seen principally with intravenous quinine, which will not be used in this study.

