## 6.5 Treatment administration and blinding

Study medications will be administered according to weight-based guidelines (Appendix 6). Study medications will not be identical in appearance or taste, but the number of doses received will be similar (2 different medicines in the morning, 1 medicine in the evening) for patients in both treatment groups. Patients will not be informed of their treatment regimen, and all study staff involved in the assessment of patient outcomes, including the study clinicians (responsible for clinical assessment and measurement of temperature) and laboratory technicians (responsible for reading thick blood smears and determining parasite density) will be blinded to the treatment group assignments

Both the morning and evening doses of the study medication will be administered in the clinic. Study medications given to young children will be crushed, mixed with water, and administered as slurry. Study medications administered to older children and adults will be given as tablets or fractions of tablets to be taken orally with a glass of water. The study nurse will directly observe consumption of study medications. Patients will be observed for 30 minutes to ensure that the medications are not vomited. Any patient who vomits the medication within 30 minutes of administration will be retreated with a second dose. Any patient who vomits repeatedly (> 3 times) will be treated with/referred for treatment with parenteral quinine and recoded as having complicated malaria.

On day 0, the first dose of study medication will be administered before 11.00 a.m. and the second dose will be administered in the evening, approximately 8 hours later. On days 1 and 2, the first dose of study medication will be administered before 9.00 a.m. and the second dose will be administered in the evening, approximately 12 hours later.

Study participants will be free to either wait at the clinic or go home and return in the evening for the evening dose of study medications. Participants who opt to wait at the clinic shall wait in a specially designated waiting area. Participants will be reimbursed for transport to and from the clinic and for lunch (those who opt to wait at the clinic for the evening dose of medications). Home visitors shall actively follow patients who do not come for scheduled appointments.

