## 7.2 Classification of treatment outcome and management of treatment failure

Patients will be followed for 28 days and will have treatment outcomes assessed according to the WHO 2003 guidelines (Appendix 7). Patients who require clinical rescue therapy (ETF, LCF, or LPF) will be treated with quinine 10 mg/kg orally three times a day for 7 days. Any patient who is diagnosed with severe malaria or danger signs during follow-up, will be referred for appropriate treatment with parenteral quinine at the local facility or hospital. Patients not admitted to the hospital will receive oral quinine to complete a 7-day course of therapy. If a patient requires clinical rescue therapy, formal study follow-up will end, and the patient will be followed up at the discretion of the study physician. Haemoglobin measurement will be repeated on the day the patient receives clinical rescue therapy.

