**ETF**

**Give/ refer for IV quinine Rx.**

Positive blood smear

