**LCF**

**Give/ refer for IV Quinine Rx.**

**ACPR** No parasitaemia on day 28 irrespective of fever history or temperature.

**LPF** Parasitaemia D 28 with temperature < 37.50C without being ETF or LCF.

# Day 2 > Day 0

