# APPENDIX 7. CLASSIFICATION OF RESPONSE TO TREATMENT

**Early Treatment Failure (ETF)**

| **ETF**   - Development of danger signs or severe malaria on Day 1, Day 2 or Day 3 in the presence of parasitemia - Parasitaemia on day 2 higher than Day 0 count irrespective of axillary temperature. - Parasitaemia on Day 3 with axillary temperature > 37.5 0C - Parasitaemia on Day 3 > 25% of count on Day 0. - Severe AE requiring change in treatment Days 0 - 2 |
| --- |

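### The quinine risk text says the intravenous route will not be used, but the protocol's own rescue flowchart directs it for smear-positive patients with severe disease or danger signs

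*Protocol*

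**What the plan says.** Section 12.2.7 lists the toxicities of quinine as a risk of taking part. It explains why quinine belongs there: "It will be the treatment for patients who fail therapy with any study regimen". It closes with "Cardiovascular toxicity is seen principally with intravenous quinine, which will not be used in this study".

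Three other places deal with the route of quinine:

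- **Appendix 4 (Critical steps).** In the branches for severe disease or danger signs with a positive smear, the early treatment failure box reads "Give/ refer for IV quinine Rx" and the late clinical failure box reads "Give/ refer for IV Quinine Rx". Other failure boxes in the same appendix specify oral quinine.
- **Section 7.2.** Rescue is oral quinine for seven days. A patient with severe malaria or danger signs during follow-up "will be referred for appropriate treatment with parenteral quinine at the local facility or hospital".
- **Section 6.5.** A patient who vomits study medication more than three times "will be treated with/referred for treatment with parenteral quinine and recoded as having complicated malaria".

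**The concern.** The closing sentence of 12.2.7 is the only mention of cardiovascular toxicity in the quinine risk text. It attributes that toxicity mainly to one route and then sets it aside because the route is said to be absent from the study. If the protocol directs that route anywhere, the reason for setting the risk aside fails.

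What is at stake is risk disclosure in a trial that enrols children aged 1 to 10 years. Section 12.4 says the consent form will describe the risks of participation, so an error in 12.2.7 could carry over into it. Site staff also face two incompatible statements on whether intravenous quinine is part of the study.

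**Working it through.** No arithmetic applies. The check is whether the statements can all be true together.

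1. **What 12.2.7 asserts.** Intravenous quinine will not be used. The statement has no qualification: it does not say that study staff will not give it, or that it is used only after referral.

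2. **What Appendix 4 directs.** The intravenous route is named twice, once for early treatment failure and once for late clinical failure. The appendix labels oral treatment separately in its other failure boxes, so the route looks deliberately specified.

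3. **Who reaches those boxes.** They follow severe disease or danger signs, an urgent smear and a positive result. Patients with a negative smear stay in the study, with treatment left to the clinician's discretion. The flowchart's connecting lines are missing from the text copy read, so the pairing of boxes is partly inferred. Appendix 7 agrees with it: its first criterion for early treatment failure is "Development of danger signs or severe malaria on Day 1, Day 2 or Day 3 in the presence of parasitemia", and late clinical failure has the matching criterion after day 3.

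4. **Whether these are study patients.** Section 4.2.1 defines clinical rescue therapy as early treatment failure plus late clinical failure, and section 4.2.2 makes its risk the primary outcome. Patients in these boxes therefore meet the definition of a primary-outcome event.

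5. **Whether rescue quinine counts as a study risk.** By its own wording, 12.2.7 includes quinine because it is the treatment for failures on either regimen. If oral rescue belongs in the risk section on that ground, so does intravenous rescue that the same protocol directs.

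6. **What 6.5 and 7.2 add.** Both say parenteral, which includes the intravenous route but is not limited to it, and 7.2 speaks only of referral. Neither contradicts 12.2.7 by itself. Both show that non-oral quinine is foreseen, and 12.2.7 describes no non-oral route as one that will be used.

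Statements 1 and 2 cannot both stand. The conflict rests on 12.2.7 against Appendix 4; sections 6.5 and 7.2 are corroboration.

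**Size.** The documents state no expected frequency of severe malaria, danger signs or repeated vomiting, so no count of exposed patients can be calculated.

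**The case against.** The best defence is that 12.2.7 means only the study's own rescue regimen, which 7.2 sets as oral, and that severe cases pass to usual care. Section 12.2.7 itself calls quinine the standard drug for severe malaria across Africa, 7.2 sends these patients to a local facility or hospital, and formal follow-up ends when rescue is needed. On that view the added research risk is small. This explains how the sentence may have come to be written, but it does not remove the conflict. Appendix 4 provides for giving as well as referring, as does 6.5, and 12.2.7 counts rescue quinine as a study risk without separating given from referred treatment. The wording does not settle who would administer the drug, so it would go too far to say that study staff will do so.

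Other parts of the defence stand:

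- The hazard is not concealed. Section 12.2.7 names it and ties it to the intravenous route; only the statement about exposure is wrong.
- A reader might infer that the review boards were misled. The documents do not support this. Section 12.1 has them review the whole protocol and the consent documents, so Appendix 4, 6.5 and 7.2 were also before them.
- A reader might infer that the planned safety comparisons suffer. The effect is slight: secondary outcomes 8 and 9 in section 4.2.3 exclude treatment failures.

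**Conclusion.** The contradiction is real and the risk text is wrong as written. Section 12.2.7 sets aside cardiovascular toxicity because a route will not be used, while Appendix 4 directs that route for smear-positive early and late clinical failures with severe disease or danger signs. A stated safety risk is thereby understated.

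The point has limits. It concerns disclosure and internal consistency, and leaves sample size, error rates and the primary analysis untouched. A reader might infer that every patient with severe illness or repeated vomiting is sent to intravenous quinine. The documents do not say so: Appendix 4 requires a positive smear, and for repeated vomiting 6.5 says only parenteral. Repeated vomiting on day 0 also fails a selection criterion in section 5.3, so those patients would not be in the retained cohort. Any figure for the number exposed would be an outside assumption.

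The conclusion rests on the flowchart boxes being paired as described, which Appendix 7 supports. The consent form was not available, so whether it repeats the statement is unknown.

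**What to change.** Reconcile section 12.2.7 with Appendix 4, 6.5 and 7.2 so that the risk section covers every route of quinine the protocol directs, and so that all four places agree on route and on whether treatment is given by the study or by referral. Which route is right is a clinical decision and is not proposed here. Check the consent text for the same statement and align it.

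The cost is about one sentence of risk text, possibly a matching sentence in the consent form, and submission to both review boards, whose approval section 12.1 requires before any amendment takes effect. No data collection, sample size or analysis needs to change.
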